# Guided Self-rehabilitation Contract *vs* conventional therapy in chronic peripheral facial paresis: VISAGE, a multicenter randomized controlled trial

**DOI:** 10.1186/s12883-023-03096-8

**Published:** 2023-04-10

**Keywords:** Facial paralysis, Rehabilitation, Neuronal plasticity, Efferent pathways, Guided self-rehabilitation contract, Motion capture, Three-dimensional, Creteil scale, Sunnybrook facial grading system, Patient health questionnaire

## Abstract

**Background:**

One year after persistent peripheral facial paresis (PFP), prescriptions of conventional rehabilitation are often downgraded into maintenance rehabilitation or discontinued, the patient entering what is seen as a chronic stage. This therapeutic choice is not consistent with current knowledge about behavior-induced plasticity, which is available all life long and may allow intense sensorimotor rehabilitation to remain effective. This prospective, randomized, multicenter single-blind study in subjects with chronic unilateral PFP evaluates changes in facial motor function with a Guided Self-rehabilitation Contract (GSC) *vs.* conventional therapy alone, carried out for six months.

**Methods:**

Eighty-two adult subjects with chronic unilateral PFP (> 1 year since facial nerve injury) will be included in four tertiary, maxillofacial surgery (2), otolaryngology (1) and rehabilitation (1) centers to be randomized into two rehabilitation groups. In the experimental group, the PM&R specialist will implement the GSC method, which for PFP involves intensive series of motor strengthening performed daily on three facial key muscle groups, *i.e.* Frontalis, Orbicularis oculi and Zygomatici. The GSC strategy involves: i) prescription of a daily self-rehabilitation program, ii) teaching of the techniques involved in the program, iii) encouragement and guidance of the patient over time, in particular by requesting a quantified diary of the work achieved to be returned by the patient at each visit. In the control group, participants will benefit from community-based conventional therapy only, according to their physician’s prescription. The primary outcome measure is the composite score of Sunnybrook Facial Grading System. Secondary outcome measures include clinical and biomechanical facial motor function quantifications (Créteil Scale and 3D facial motion analysis through the Cara system), quality of life (Facial Clinimetric Evaluation and Short-Form 12), aesthetic considerations (FACE-Q scale) and mood representations (Hospital Anxiety and Depression scale). Participants will be evaluated every three months by a blinded investigator, in addition to four phone calls (D30/D60/D120/D150) to monitor compliance and tolerance to treatment.

**Discussion:**

This study will increase the level of knowledge on the effects of intense facial motor streng-         
Facial paralysisthening prescribed through a GSC in patients with chronic peripheral facial paresis.

**Trial registration:**

ClinicalTrials.gov, NCT04074018. Registered 29 August 2019.

**Protocol version:**

Version N°4.0—04/02/2021.

**Supplementary Information:**

The online version contains supplementary material available at 10.1186/s12883-023-03096-8.

## Background

Peripheral facial paresis (PFP) is a common disorder, which often affects adults between 40 and 50, with no gender predominance. PFP results from an injury to the facial nerve, from its pontine nucleus to its neuromuscular junctions; its severity depends on lesion location, cause and degree of injury. Seventy percent of cases are idiopathic, called Bell’s palsy, with a lifetime incidence of 1 in 60 people [1], representing an incidence of 15 to 50 new cases for 100 000 persons per year [1, 2]. In 70–90% of cases, recovery to baseline occurs within 6–9 months [3–6]. The other 10–30% enter a chronic stage with one of two clinical forms: a non-overactive form with flaccidity of the paretic hemiface, described as a global loss of tone, and an overactive form mixing paresis and facial involuntary muscle overactivity in the affected hemiface [7]. Muscle overactivity may occur at rest through involuntary tonic contractions of some facial muscles, called facial dystonia, or through small brief contractions known as facial spasms. Muscle overactivity may also occur during movements, manifesting as facial cocontractions known as synkinesis. These persistent motor signs strongly impede quality of life, aesthetically and psychologically [8, 9].

Regarding clinical evaluation of PFP, heterogeneity in assessments makes comparisons between various interventions difficult [10]. The classic House-Brackmann Grading Scale is still used in clinical practice but no longer recommended due to inadequate psychometric characteristics, regarding its validity in particular [10, 11]. In 2015, the *Sunnybrook Facial Grading System* (SFGS) was suggested as a new standard in reporting outcomes of facial nerve injuries [10, 12]. Additional criteria for grading were later added to improve its reliability [13]. Nevertheless, evaluations through SFGS have four important limitations: i) the scale remains an ordinal grading system with few grades, lacking accuracy and thus jeopardizing responsiveness; ii) it investigates only five facial muscle groups, among over twenty muscle groups on each hemiface, omitting platysma for example; iii) it does not assess spontaneous and/or conversational facial movements even though this is the main function of the facial nerve, i.e. to reflect our emotions; iv) it is not systematically video-recorded, precluding retrospective checking and visual follow-ups. Recently, a Delphi study on consensus research priorities for facial palsy insisted on standardization of clinical assessments as a high priority for both patients and healthcare professionals [14].

In terms of rehabilitation, evidence from randomized controlled trials (RCT) is still insufficient, partly because of this lack of precise and objective quantification tools for facial motor function. Most publications on facial rehabilitation pertain to acute and subacute stages of PFP and involve prescriptions for physical therapy and/or speech therapy [15]. The rehabilitation techniques used are varied and heterogeneous, and consensus is lacking. A longstanding, classic principle has been to avoid muscle strengthening exercises and facial muscle electrical stimulation, especially in acute stages, for fear of generating muscle overactivity [15]. Yet, RCTs involving active motion exercises in acute stages have shown improved recovery, particularly in severe cases, with no increase—or even a decrease—in synkinesis [16, 17]. As for electrical neurostimulation of the facial nerve, despite also being controversial in acute stages [18], both classic and recent evidence from controlled literature favors either no effect or a positive effect with respect to synkinesis [19–21].

To our knowledge, there is no RCT analyzing motor strengthening in chronic stages (> 1 year since injury), when motor impairments are often considered permanent [20]. In other fields of neurorehabilitation, a considerable body of evidence shows that high intensity of rehabilitation (the opposite of “maintenance therapy”) is associated with improvement of motor function in chronic stages, via enhanced brain plasticity [22–25], specifically *behavior-induced plasticity*. The reality and potentially powerful effects of behavior-induced neural plasticity have been first demonstrated in the early twentieth century by Pavlov—under the misleading name of *conditional reflexes*—and its synaptic mechanisms have been elucidated by Kandel [26]. Behavior-induced plasticity involves changes in synaptic sensitivity, in neuronal connections or in cell numbers resulting from changes in environmental conditions, including behavioral changes, such as engagement into an intensive facial rehabilitation program. Such program may have the capacity to place cortical, sub-cortical, brainstem and peripheral nervous system regions under sufficient constraint, so as to strengthen and facilitate the command to facial muscles [25, 27]. Behavior-induced plasticity may take over after the end of the period of lesion-induced plasticity, which typically runs for few months after the lesion [28]. One way to achieve sufficient amounts of physical treatment might be to adequately *motivate and guide* the patient to practice self-rehabilitation. It has been confirmed that programs of exercises given by the therapist to be performed at home are appreciated by patients not only for the structure they give to everyday life, but also as they represent in themselves a source of motivation and hope, particularly when these programs are associated with ongoing professional support [29, 30].

The government-funded VISAGE project is a French multicentric RCT in which 82 patients with chronic stable unilateral PFP of any cause will be randomized into two six-month rehabilitation programs – motor strengthening through Guided Self-rehabilitation Contract *vs.* conventional therapy – to compare their effects on facial motor recovery. Once past the stages of lesion-induced nervous system plasticity, we hypothesize that behavior-induced plasticity will be stimulated through intensive motor strengthening rehabilitation work in chronic PFP using a Guided Self-rehabilitation Contract.

### Objectives

The primary objective of this study is to evaluate changes in subjective facial motor function after six months of Guided Self-rehabilitation Contract compared to conventional therapy alone, in chronic stages following facial nerve injury. Secondary objectives include the evaluation of differences in changes between the two treatment groups in: i) specific PFP-related quality of life; ii) overall quality of life; iii) aesthetic considerations; iv) mood; v) objective 3D facial motor function.

## Methods/design

### Ethical approval and trial registration

The VISAGE study has been designed in accordance with the Helsinki Declaration. The study protocol, patient information letter, and informed consent form have been approved by the Institutional Review Board ‘Est-III’ (Nancy, France) on October 3^rd^ 2018. The VISAGE study is registered in the ClinicalTrials.gov database (NCT04074018).

### Research design

VISAGE is a single-blind, prospective, controlled, randomized multicenter study in 82 participants with chronic unilateral peripheral facial paresis (> 1 year since facial nerve injury). The trial will be run in four tertiary centers, including maxillofacial surgery (2), otolaryngology (1) and neurorehabilitation (1) units. For all participants, the study will begin at inclusion (Day-30). At that time point, the investigator will implement computerized randomization to assign a group treatment to the patient, between Guided Self-rehabilitation Contract (GSC) and conventional therapy (CONV) alone, for six months. A delay of one month between inclusion (D-30) and the first assessment (D1) is anticipated to account for the time to find a therapist and to ensure timely rehabilitation onset (D1) for the participants in the CONV group. In the GSC group, the participants will be free to continue potential preexistent conventional therapy if there was any. The total duration of subject participation in the study is seven months. Study data will be analyzed through intention-to-treat and per-protocol analyses.

### Interventions

#### Conventional therapy

In the Conventional Physical Therapy group (CONV), the study PM&R specialist prescribes physiotherapy and/or speech therapy sessions at inclusion (D-30), for a six-month period starting at D1. For this purpose, a list of physical and speech therapists specialized in PFP rehabilitation and working in the Greater Paris area is provided to each subject. Each therapist of that list has personally agreed to potentially take care of patients of the VISAGE study in due course. Such community-based therapy sessions are universally and indefinitely covered by public health insurance in France. Whichever the study group, subjects already undergoing community-based rehabilitation are free to pursue that rehabilitation during the six months of the study. Indeed, the discontinuation of previous rehabilitation might lead to nocebo effects, which is well known in rehabilitation RCT studies [31, 32]. The treatment of the control group is intended to reflect the usual management of patients with chronic peripheral facial paresis. The physiotherapists caring for the patients in the control group are all trained in the rehabilitation of facial paresis and accustomed to treating this disorder. As mentioned above, there is no standardized rehabilitation protocol and the techniques are diverse and heterogeneous among therapists. Each practitioner in the control group therefore chooses the frequency of the rehabilitation sessions, the techniques used and the duration of each rehabilitation session. Such information will be noted however, by the study examiners to quantify and qualify the control group rehabilitation.

#### Guided self-rehabilitation contract

In the GSC group, patients will be free to follow any conventional community-based therapy sessions, as in the CONV group. In addition, in the evaluation center, the study PM&R physician will provide three one-hour rehabilitation clinic visits at D1, D90 and D180, with the following objectives:*Explain the principles of the Guided Self-Rehabilitation Contract* to the patient. The GSC is a diary-based program centered on a moral contract in which each party, study participant and PM&R physician or GSC therapist, commits to the other on the following actions. The PM&R physician or GSC therapist commits to:*Prescribe* and *teach* a daily program of facial muscle strengthening exercises customized to the participant (see Figs. 1 and 2), and adjust the techniques according to clinical progress. Here, the study PM&R physician will provide a manual to the subject, which contains the prescribed program, with illustrations of the training exercises. Three facial muscle groups are targeted, selected because of the low risk of apraxia for the command to these muscles in the general population [33] and their localization (one for each third of the face): Frontalis, Orbicularis oculi and Zygomaticus. For each muscle group, the training program consists of three daily series of bilateral unassisted repeated efforts or movements of maximum amplitude until *fatigue* (e.g. 20 to 40 facial contractions per series, depending on fatigability). We have thus chosen to strengthen these three facial muscle groups that are crucial for facial motor function: raising eyebrows (expressiveness), closing eyes (eye protection) and smiling (communication, emotional expression, interaction with others). In practice, these muscles are easy to reach using voluntary command and therefore to rehabilitate. Each of them is located on one of the three vertical thirds of the face: during these efforts, several facial nerve branches covering the entire face are therefore stimulated from the top to the bottom of the face. Each branch of the facial nerve innervating several facial muscles, we postulate—and see in routine practice—that participants will also improve on neighboring muscles not directly targeted by the strengthening.*Request a diary* from the patient at each visit, in which the daily number of efforts or movements performed in each series in the interval between two visits with the PM&R physician should be recorded (Fig. 3). The PM&R physician stresses to the subject that such *self-monitoring* through the quantified written diary actually *belongs* to the therapy, in other words that the same physical exercises without maintaining the diary are likely to not carry the same efficacy [34–43]. Indeed, written feedback from patient to therapist/physician improves compliance to the self-rehabilitation program and thus the efficacy of this program [34–39]. Most importantly, the diary provides the patient with positive reinforcement, with potentially enhanced motor circuit excitability and even antidepressant effects [40–42, 44]. Regardless of self-monitoring, quantitative feedback on performance provided to the patient has been shown to improve rehabilitation effectiveness during the subacute phase of stroke [43].*Verify* patient compliance to the prescribed program by ensuring that the self-rehabilitation diary is well kept. The study physician will count the number of filled out days in the diary and divide it by the number of elapsed days since the last visit. In return, the subject commits to performing the prescribed daily self-rehabilitation program, including in particular the production of the written diary of exercises and to return it at each visit.

**Fig. 1 Fig1:**
[figure not shown]
Prescription of the Guided Self-rehabilitation Contract

**Fig. 2 Fig2:**
[figure not shown]
Self-rehabilitation techniques included in the Guided Self-Rehabilitation Contract

**Fig. 3 Fig3:**
[figure not shown]
Template of diary for the Guided Self-rehabilitation Contract

### Outcome measures

To evaluate motor function beyond one year after facial nerve injury, the primary outcome measure will be the composite score of the Sunnybrook Facial Grading System. This scale, created by Ross et al. in 1996, assesses resting symmetry compared to the normal side for each third of the face through rating of resting symmetry, of symmetry of voluntary movements on a five-grade scale during five facial movements, and associated synkinesis. A composite score is then calculated, ranging from 0 (total paralysis) to 100 (normal) [12]. The French version of the SFGS was recently validated [45]. As stated above, the choice not to use House-Brackmann evaluation scales [11, 46] is in accordance with the fact that these scales are no longer recommended in research [10, 47, 48].

Secondary outcome measures will include:Specific PFP-related quality of life evaluated through the Facial Clinimetric Evaluation (FaCE), a self-questionnaire validated in French [49]. The FaCE studies specific quality of life for PFP patients through 15 items evaluating six domains [50].Overall perceived quality of life evaluated through the Short Form version 12 (SF 12): this is a self-questionnaire comprising 12 items evaluating quality of life. The scoring system is ordinal. Two scores are calculated, a Physical Composite Score (PCS on 26) and a Mental Composite Score (MCS on 30) [51]; the SF 12 was validated in French in 1998 [52].Aesthetic self-assessment collected using the FACE-Q scale; this is a ten-item self-questionnaire questioning the patient on facial aesthetics [53, 54]. The scoring system is ordinal from 1 (« very unsatisfied») to 4 (« very satisfied»); it has been validated in 2022 [55].Anxiety and depressive disorders using the Hospital Anxiety and Depression Scale (HADS): [56]; this self-questionnaire includes 14 items rated from de 0 to 3. Seven items are related to anxiety and seven to depressive features, leading to 2 final scores (/21). Scores of 7 or less indicate a lack of symptoms, 8 to 10 suggest questionable symptomatology and 11 and more attest to definite symptomatology. The scale has been validated in French in various patient populations [57].Evaluation of compliance to and amount of self-rehabilitation in the GSC group, through the filling ratio of the diary over six months.Evaluation of the amount and type of conventional therapy in both groups, through collected data on the mean frequency and techniques used over six months.Subjective facial motor function quantification during the Créteil Scale. The Créteil Scale (CS) has been developed by [name] and [name] in 2012 [58] to assess 12 groups of facial muscles: frontalis, corrugator, procerus, orbicularis oculi, canine, zygomaticus, risorius, buccinator, orbicularis oris, depressor anguli oris, mentalis, and platysma. For each of these 12 muscle groups, the scale quantifies five fundamental components of facial nerve injury, at rest, during maximal effort and during spontaneous conversation: 1) *Motor strength* of the 12 facial muscle groups rated through a 9-grade scoring system from 0 (no contraction) to 3 (normal contraction); 2) Localization and intensity of involuntary *synkinesis* generated during maximal voluntary effort directed to each of the facial muscle groups; 3) Localization and frequency of involuntary *spasms* during a 30-s resting period *and* during a 30-s spontaneous conversation period, rated through an ordinal 7-grade scoring system; 4) A *paresis-related symmetry score*, quantifying symmetry at rest and during conversation searching for lacks of contraction of each muscle group; 5) A *dystonia-related symmetry score*, quantifying symmetry at rest and during conversation searching for overactivity in each muscle group. This study will explore the validity, intra- and inter-rater reliability of the Créteil Scale, as well as its responsiveness to rehabilitation in a chronic stage.Objective 3D facial motor function quantification through 3D wearable (helmet) facial motion analysis through the Cara™ system. Asymmetry ratios and Procuste analysis will be performed at rest (during a 30-s period), during twelve maximal movement efforts and during spontaneous smile [59]. Measurement of the amount of synkinesis during voluntary movement, of spasms and dystonia at rest will also be performed using Procuste distances: synkinesis (quality, frequency and severity) will be assessed during each maximal voluntary movement (12 movements in total) and during one spontaneous smile; spasms will be assessed during a 30-s period of rest, as well as dystonia.

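### The amount of self-rehabilitation in the GSC group is assigned to a ratio of diary days, which can describe diary keeping but cannot measure amount

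*Protocol article*

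**What the plan says.** The Outcome measures section of the protocol article lists as one secondary outcome: "Evaluation of compliance to and amount of self-rehabilitation in the GSC group, through the filling ratio of the diary over six months". Two targets, compliance and amount, are given one metric.

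The section on the Guided self-rehabilitation contract says how the metric is obtained: "The study physician will count the number of filled out days in the diary and divide it by the number of elapsed days", counted from the previous visit. It gives no minimum content for a day to count as filled out.

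The same section describes the programme. It says "Three facial muscle groups are targeted", and then "For each muscle group, the training program consists of three daily series of bilateral unassisted repeated efforts or movements of maximum amplitude until" fatigue, with an example of "20 to 40 facial contractions per series, depending on fatigability". The programme is customised to the participant and adjusted with progress. The diary is meant to hold more than a tick per day: it is to contain "the daily number of efforts or movements performed in each series in the interval between two visits". Table 2 schedules review of the diary at D90 and D180.

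**The concern.** An outcome should measure what it is named for. A share of days carries no information on how many series or movements were done on a day, so it has no means of expressing amount. The counts that would express it are requested in the diary, but the stated outcome does not use them.

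This matters here because intensity is the trial's argument. The Background hypothesises that intensive strengthening work stimulates behaviour-induced plasticity. The Discussion section on the two rehabilitation groups argues that usual practice avoids intensity and presents a higher work level as central to the GSC. For conventional therapy, the plan collects mean frequency and techniques in both groups. For the experimental programme itself, the only stated summary is the day ratio. Reported that way, a null result could not be told apart from low delivery, and a positive result could not be related to the quantity of work done.

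**Working it through.** The article gives no numerical value for this outcome, so there is no figure to reproduce. The check is whether the stated metric can track its named target.

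**Inputs** (all from the section on the Guided self-rehabilitation contract)
- Muscle groups: 3. Daily series per group: 3.
- Movements per series: 20 to 40, given only as an example that depends on fatigability.
- Filling ratio: r = filled-out days / elapsed days.
- Elapsed days, D1 to D180: taken as 180, a round figure.

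**Programme as described**
- Series per day: 3 × 3 = 9. Over 180 days: 9 × 180 = 1,620.
- Movements per day: 9 × 20 = 180 to 9 × 40 = 360. Over 180 days: 32,400 to 64,800.

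**What a given ratio says about series.** Suppose a day counts as filled out when at least k of the nine series are entered. The article does not fix k, so it is an assumption, varied here from 1 to 9. A counted day then holds k to 9 series and an uncounted day 0 to k − 1. Mean recorded series per day therefore lies between r × k and r × 9 + (1 − r) × (k − 1).

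| Reading | r = 100% | r = 50% |
|---|---|---|
| Any entry suffices (k = 1) | 1 to 9 | 0.5 to 4.5 |
| All nine needed (k = 9) | 9 | 4.5 to 8.5 |

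Only in one cell, the strictest reading at 100%, does the ratio fix the number of series. Even there it does not fix movements: 180 and 360 per day give the same ratio.

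**Whether the ratio orders patients correctly** (30 movements per series assumed throughout)
- Any entry suffices. Patient A does one series on 180 of 180 days: r = 100%, movements 1 × 30 × 180 = 5,400. Patient B does nine series on 90 of 180 days: r = 50%, movements 9 × 30 × 90 = 24,300. B does 24,300 / 5,400 = 4.5 times the work at half the ratio.
- All nine needed. Patient C does eight series on 180 of 180 days: r = 0%, movements 8 × 30 × 180 = 43,200. Patient B keeps r = 50% with 24,300. C does 43,200 / 24,300 = 1.8 times the work and scores zero.

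The ordering can reverse at either extreme of the definition, so settling the definition of a filled-out day would not by itself make the ratio a measure of amount.

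**The case against.** The strongest case against is that little here is firmly wrong. A filled-out day is not defined, the diary template (Fig. 3) is not shown, and how diary counts become an analysis variable is detail that an article may leave to the full protocol or analysis plan. The filling ratio also has a proper role: the article treats self-monitoring through the diary as part of the therapy, so the ratio measures adherence to a real component. Compliance is followed by four phone calls as well.

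Most of that stands, and it rules out several stronger readings that a reader might infer.

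- **That the plan scores a one-series day the same as a nine-series day.** No section says so. It is one possible reading of an undefined term; the check is described as whether the diary is well kept, and a nearly empty day might not pass.
- **That a full ratio hides an 18-fold range of work** (360 / 20). This compares one series of 20 with nine of 40. The factor of two between 20 and 40 is intended, since series run to fatigue; the remaining factor of nine depends on the undefined term.
- **That the counts are thrown away.** The article does not say they will go unentered. It says only that the outcome is obtained through the ratio. Because the counts are in the diaries, the delivered amount is recoverable.
- **That the per-protocol population rests on this ratio.** The article plans per-protocol analyses but nowhere ties that population to diary filling.
- **That the ratio is a wrong measure of compliance.** It is sound for diary keeping.

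What the objection does not remove is the sentence in Outcome measures. It is a stated rule, not an omission: it names amount as a target and assigns it to a ratio of days. No diary layout and no definition of a filled-out day turns that ratio into an amount.

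**Conclusion.** The point holds in a limited form. The secondary outcome on compliance and amount in the GSC group is defined solely through a ratio of days. That ratio can describe diary-keeping compliance and cannot measure amount under any reading of a filled-out day.

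The size is illustrative. If any entry suffices, a ratio of 100% is compatible with one to nine series per day; if all nine are required, series are fixed at 100% but not below it, and movements are never fixed. These ranges rest on the default programme of nine series, the example of 20 to 40 movements per series, and 180 elapsed days.

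The consequence is confined to a descriptive process measure in one arm and to any dose-response or predictor analysis that might use it. The primary intention-to-treat comparison and the sample size are not touched. The change is worth making because it is inexpensive and the trial's rationale is intensity.

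**What to change.** 1. Keep the filling ratio, label it as compliance with diary keeping, and state what makes a day filled out.
2. Define amount separately: recorded series and recorded movements per elapsed day, by muscle group, over D1 to D180.
3. Express series compliance as recorded series over the series prescribed to that patient, nine per day by default. A fixed denominator of nine for everyone would ignore that programmes are customised and adjusted.
4. Report days without an entry as unrecorded. Counting them as zero work is one assumption, to be stated as such, since exercise may have been done and not written down.
5. Use the amount measure, not the filling ratio, in any dose-response or predictor analysis of change.

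**Cost.** No new data collection and no change to treatment. The work is entering or totalling the counts from diaries already reviewed at D90 and D180, plus a few lines of wording in the protocol or analysis plan.
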